## Secondary outcomes

Demographic information including falls history (and associated information surrounding circumstances of falls), duration of joint symptoms, comorbidities, medical conditions and medications will be collected.

The following functional, physiological and cognitive tests will be assessed at baseline and at the follow-up assessment. These selected tests are key measures used to identify risk of falls:Leg strength and endurance will be assessed using the 30 s chair stand test. Participants will sit on a chair (a 43-cm high chair) and stand up, then repeat, as many times as they can for 30 s (no upper limb support), the number of sit to stand efforts performed will be recorded [21]Physical function will be assessed using the Timed Get Up and Go Test (with and without dual tasks (manual and cognitive)) [22]. Participants will stand up from a chair, walk 3 m as quickly and safely as possible, cross a line marked on the floor, turn around and walk back and sit down. This test will also be performed when carrying a glass of water (manual dual task) and when counting backward by 3’s (cognitive dual task). The time taken to complete the task will be measured with a stopwatch. One practice trial will be given followed by an actual testA rapid dynamic weight shift, coordination and stepping will be assessed using The Four Square Step Test (FSST) of balance [23]. Participants will step as fast as possible into four squares marked on the floor with tape (labeled 1–4) in a certain sequence (starting from square 1 then 2, 3, 4, 1, 4, 3, 2 and 1). This sequence requires the participant to step forward, backward, and sideways to the right and left. The score will be recorded as the time taken to complete the sequenceFunctional muscle power will be assessed using the Timed Stair Climb Test (10 steps, 14-cm rise). The time taken to complete the task (climb 10 steps as quickly as possible) will be recorded and the stair climbing power will be calculated using a formula described in previous research [24]Static balance will be assessed by evaluating postural sway of the body in the medio-lateral (M/L) and anterior posterior (A/P) directions using a swaymeter while standing on a medium-density foam rubber mat (70 × 60 × 15 cm thickness) with the eyes open and closed. The total excursion of the sway in each direction is measured in millimeters [25]Knee proprioception will be measured during sitting by matching the position of the legs on either side of a clear plastic sheet with the eyes closed [3]. Any error in matching the limbs will be recorded in degrees. After two practice trials, the average of five trials will be recordedThe ability of older people to step maximally and rapidly in multiple directions will be assessed using the Maximum Step Length and Rapid Step Test [26]. Initially, the maximum step length in the front, side and back directions will be assessed. With arms crossed over the chest, the participant will step maximally with one leg while keeping the other leg planted and then to return to the initial position in one step. The test will be repeated for each leg in three directions (front, side, back). Three practice trials will be given followed by a series of five trials for each leg in each direction. The step length will be measured and the average of the five trials will be used for the rapid step test. For the rapid step test, marks on the floor will be placed at 80% of the maximum step length measured previously in each direction. Participants will then step as fast as possible with one leg in a given direction on the marks on the floor as instructed by the assessor. A practice set of four steps for each leg will be given. The actual testing will include a series of 24 steps randomly selected by the assessor which will include four steps in each direction for each leg. The total time taken to complete the step sequence and any errors will be measured. An error will be defined as (1) loss of balance, (2) failure to return to the initial position, (3) multiple steps and (4) noncompliance with direction or sideLower-limb muscle strength will be assessed by having participants perform three maximal repetitions (3RM) during bilateral leg press using a seated leg-press machine. The maximum amount of weight lifted by participants through three full-range repetitions while maintaining correct technique will be used for determining the participant’s maximum 3RM strength. Participants will have a familiarisation session before the actual recording of the 3RM test. During the familiarisation session participants will be shown the correct exercise technique and be given the opportunity to familiarise themselves with the exercise. Initially, each participant will perform a warm-up set of eight repetitions on the leg press with a light load. This will then be followed by the completion of five to six repetitions at a heavier weight and rest period of 2–3 min. The load will be increased incrementally until only three repetitions with correct technique are able to be completed

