**Fig. 2 Fig2:**
[figure not shown]
Study design schedule in accordance with the Standard Protocol Items: Recommendations for Interventional Trials (SPIRIT) Figure

Participants will first attend the Victoria University Footscray Park campus for baseline testing. During the first visit all measures, excluding strength, will be assessed. Familiarisation with the strength test will be conducted in the first visit followed by actual testing during a second visit (approximately 3–6 days apart). A set of questions to assess cognitive impairment (memory) will also be conducted in the initial visit using the SLUMS test where participants who score below 25 cut-off scores will be excluded from the study [11]. In the second visit, after completion of the strength test, participants will be randomized to one of the three groups: (1) high-speed resistance-training (HSRT) or (2) high-speed resistance-training and balance exercises (HSRTB) or (3) control group (no intervention). All eligible participants will complete the Exercise and Sport Science Australia (ESSA) exercise screening tool to evaluate any contraindicated medical conditions to exercise (https://www.essa.org.au/wp-content/uploads/2011/09/Screen-tool-version-v1.1.pdf). Participants answering “yes” to any of the screening questions will be required to obtain medical clearance from their local physician prior to participation in the intervention. Only participants randomized to one of the exercise intervention groups will need to obtain medical clearance if deemed relevant. Participants in the exercise intervention groups will attend Victoria University Exercise Rehabilitation Clinic twice a week for 8 weeks (total of 16 exercise sessions). Participants from the control group will be advised to continue with their usual activities. All participants will be reassessed after 8 weeks from the baseline assessment.

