### Randomisation

All participants will be randomly allocated to one of the following groups: (1) HSRT or (2) HSRTB or (3) control group (no intervention). Block randomisation will be undertaken using opaque envelopes, so that blocks of six to seven participants (two to three for each intervention group and two to three for control group) will be randomized at a time. As participants will either be doing one of two different exercise programs or not doing an exercise program, assessors and participants will not be blinded to their respective group allocation.

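### The Rapid Step Test is scored on total time, but its step order is left to the assessor, who knows the arm at week 8

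*Protocol article*

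**What the plan says.** The Secondary outcomes section describes the Rapid Step Test. Floor marks are set at 80% of each participant's maximum step length. The participant then steps as fast as possible "on the marks on the floor as instructed by the assessor". On the content of the test: "The actual testing will include a series of 24 steps randomly selected by the assessor". The article also fixes the mix of those steps, though not their order: "which will include four steps in each direction for each leg". On the score: "The total time taken to complete the step sequence and any errors will be measured". A step in the wrong direction or with the wrong leg counts as an error.

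The same section also times the Four Square Step Test, and there it prescribes one order for everyone: "in a certain sequence (starting from square 1 then 2, 3, 4, 1, 4, 3, 2 and 1".

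The Randomisation section states that "assessors and participants will not be blinded to their respective group allocation". The Procedure section (text after Fig. 2) fixes the sequence of events. For the first visit: "During the first visit all measures, excluding strength, will be assessed". Then: "In the second visit, after completion of the strength test, participants will be randomized to one of the three groups".

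The Statistical analysis approach section plans a repeated-measures ANOVA of group by time for selected outcomes, to look for trends and to supply power calculations for a later trial.

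**The concern.** In a timed test, whatever the assessor varies becomes part of the measurement. Here the assessor selects the order of the steps and instructs the participant, and the result is elapsed time. Two effects have to be kept apart.

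- **Noise.** If some orders are harder than others, a participant's change from baseline to week 8 includes the difference in difficulty between two unrelated orders. With 10 participants per arm, such noise does not average out well. It also enters the SD carried into the future trial's sample size.
- **Possible bias at week 8.** By then the assessor knows the arm. Cueing that is a little brisker in an exercise arm, or an order that is not truly random, would read as faster stepping.

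The outcome lies close to the trial's rationale: the Background section gives slower step responses as one of the impairments behind falls in knee osteoarthritis.

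**Working it through.** **Inputs from the protocol article.** Four steps in each of three directions for each of two legs; total time as the score; 10 participants per arm; unblinded assessors; baseline test at visit 1 and randomisation at visit 2.

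**Inputs assumed, because the documents give none.** Time cost of a leg change (0.1 to 0.5 s); difference in cue delay per call (0.05 to 0.2 s); SD of the analysed change (3, 5 or 8 s).

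**1. The plan's own figure.** 4 × 3 × 2 = 24 steps, which reproduces. Content is therefore fixed and only order is free. The number of distinct orders is 24!/(4!)^6 ≈ 3.2 × 10^15.

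**2. How much random orders differ.** With 12 steps per leg, the number of leg changes is the number of runs minus one.

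- Mean: 2 × 12 × 12/24 = 12
- Variance: 288 × (288 − 24)/(24² × 23) = 288 × 264/13,248 = 5.74, so SD = 2.40

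A simulation of 50,000 random orders agrees: mean 12.0, SD 2.4, 95% range 7 to 17. Changes of target (leg or direction) average 20.0, SD 1.6, range 17 to 23.

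**3. Noise from order.** If each leg change costs c seconds, order contributes an SD of 2.40c to one test and 2.40c × √2 to a change score.

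- c = 0.1 s: 0.24 s per test, 0.34 s on the change
- c = 0.5 s: 1.2 s per test, 1.7 s on the change

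The added variance of the change is 2 × c² × 5.74, that is 0.115 s² for c = 0.1 s and 2.87 s² for c = 0.5 s. As a share of the variance without order noise:

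| Assumed SD of change | c = 0.1 s | c = 0.5 s |
|---|---|---|
| 3 s (variance 9) | 1.3% | 32% |
| 5 s (variance 25) | 0.5% | 11% |
| 8 s (variance 64) | 0.2% | 4% |

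A sample size based on this outcome rises by the same percentage.

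**4. Possible bias from cueing.** If each step is called, a mean difference of d seconds per call shifts total time by 24d: 1.2 s, 2.4 s and 4.8 s for d = 0.05, 0.1 and 0.2 s. With no true effect, the chance that a two-arm comparison reaches two-sided p < 0.05 in the direction of the shift is about Φ(24d/(SD × √(2/10)) − 1.96). With no shift it is 2.5%.

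| Assumed SD of change | d = 0.05 s | d = 0.1 s | d = 0.2 s |
|---|---|---|---|
| 3 s | 14% | 43% | 95% |
| 5 s | 8% | 19% | 57% |
| 8 s | 5% | 10% | 27% |

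For example, d = 0.1 s and SD 3 s: 2.4/(3 × 0.447) − 1.96 = −0.17, giving 43%. The results run from negligible to serious depending on inputs that the documents do not supply.

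**5. When knowledge of the arm can act.** The baseline test belongs to visit 1 and randomisation to visit 2. The arm does not exist at baseline, so only the week-8 test is exposed.

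**The case against.** The strongest reply is that several readings a critic might adopt go beyond the text.

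- **A reader might infer that the assessor improvises the order on the spot and sets a calling pace.** The article says neither. An order drawn at random beforehand fits its wording equally well, and no cueing procedure is described. Cue timing is the kind of operating detail that an article may leave to the full protocol or to the cited source of the test. Its absence is not in itself a fault.
- **A reader might infer that both assessments are made with the arm known.** The Procedure section rules this out for baseline.
- **A reader might infer that random order favours an arm.** It does not. A truly random order adds variance only. Bias needs cueing or ordering that depends on the arm, and such ordering would depart from the stated random selection.
- **A reader might take the figure of 2.4 s as an estimate.** It needs the same assumed 0.1 s difference on all 24 calls. Nor do the documents show that changing legs costs time, since the participant must return to the starting position after each step anyway.

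All of this stands and limits the point. What remains is a stated procedure, not a silence: the assessor selects the order and the score is elapsed time. The neighbouring Four Square Step Test shows that the article does fix an order where it chooses to. Calling step by step is also the natural reading, since 24 randomly ordered steps could hardly be done from memory and a wrong direction or leg is scored as an error. Nor is this only the general lack of blinding: a blinded assessor at week 8 would remove the arm-related part but not the order noise.

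**Conclusion.** The point holds in a limited form. Order is uncontrolled between visits and participants, which adds noise to the pre-post change if orders differ in difficulty. Under the assumed leg-change costs this is an SD of 0.34 to 1.7 s on the change. Bias is possible only at week 8, and only if cueing or ordering depends on the arm. Its size cannot be determined from the documents, and they give no evidence that it occurs.

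The consequence is confined to one secondary outcome in a pilot whose primary measures are feasibility and safety. The analysis section does not name this test among its examples. What could be affected is any trend reported for the test, and the effect and SD taken from it into the later trial's power calculation. This is a minor improvement, worth making because it is nearly free.

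**What to change.** Replace the clause that has the assessor select the steps at random with the following:

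1. Two pre-generated 24-step sequences, each with four steps per direction per leg and matched on the number of leg changes and direction changes.
2. Counterbalanced order of the two sequences across the two visits within each arm, from a list prepared in advance. With 10 per arm, five participants would have each order. Giving everyone one sequence at baseline and the other at week 8 would not do, because any leftover difference in difficulty would be confounded with time in the planned within-group comparisons.
3. Each cue given at one fixed event, the foot back at the start position.

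The baseline test precedes randomisation, so the sequence order must be assigned before the arm is known. Exact balance within arms would need sequence order as a stratum for the envelopes. Otherwise the balance holds only on average.

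The cost is two printed sheets, one counterbalancing list and a sentence or two of text. Recruitment is described as ongoing, so the change can start with participants not yet tested at baseline, which keeps each participant's two tests on the same method.

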
### Cognitive tests – assessment of executive function

Exercise is associated with an improvement in cognitive performance [27], most notably executive functions. Executive function is a psychological construct used to describe cognitive processes that enable the formation, planning, execution and monitoring of goals. The processes involved include inhibitory control, working memory and cognitive flexibility [28]. The neuropsychological assessment instruments that will be used to assess executive functions of set switching, inhibition and updating/working memory [29, 30] will include *The Trail Making Test* (*TMT*) [31], *The Wechsler Adult Intelligence Scale-III* (*WAIS-III*) [32] and *The Stroop Color* and *Word Test Victoria Version* [33]. These tests are commonly used in research and have demonstrated reliability and validity for this age group.Set-shifting and psychomotor speed will be assessed using The Trail Making Test (TMT). The TMT is a two-part (TMT-A and TMT-B) assessment of general brain function. The TMT-A requires participants to connect numbers with a line, while the TMT-B requires both letters and numbers to be connected. TMT-A assesses visuo-perceptual and motor abilities, while the TMT-B assesses working memory and task-switching ability [31]. Participants will be administered a pen-and-paper version of the TMT, which takes 5–10 min to completeWorking memory will be assessed using The Digit Span Task from The Wechsler Adult Intelligence Scale-III (WAIS-III). The WAIS-III is a widely used battery of tests that assesses different aspects of adult human intelligence [32]. Each task has a forward and backward version. In the Forward Digit Span Task the respondent is verbally presented with a string of numbers by the examiner and is asked to repeat them back exactly as they were presented. The string of numbers starts at two and continues until the respondent fails to repeat the correct sequence of numbers on both attempts. The Backwards Digit Span Task requires the respondent to repeat the string of numbers in the reverse order. Two trials of each span length will be attempted. The task is discontinued if the respondent fails to repeat the correct sequence on both attemptsSelective attention, response inhibition and speed of processing will be assessed using The Stroop Color and Word Test Victoria Version [33]. The test has three pages. The first page has colour names printed in black ink. The second page has X’s printed red, blue or green and the third page has colour names printed in contrasting colours; for example, the word “green” printed with red ink. The assessor will ask the respondent to read the words on page one or name the colours on pages 2 and 3 as quickly as possible within a 45 s time limit. The instructions for pages 2 and 3 require the respondent to inhibit the automatic response to say the word and instead name the colour. Scores are compared to normative data

### Health-related quality of life questionnaires

*Joint pain and function* will be assessed using the Western Ontario and McMasters University Osteoarthritis Index (WOMAC) [34]. The WOMAC is a self-assessed disease-specific measure of patients with OA of the hip and knee. This index assesses the severity of the knee pain during five daily activities and the severity of impairment of lower-extremity function during 17 activities. The items are scored with the use of a 10-cm Visual Analogue Scale, where 0 represents no pain or difficulty with physical function, with higher scores representing worse functional health
*Quality of life* will be measured using the self-administered Assessment of Quality of Life (AQoL) utility instrument, which assesses quality of life over five domains including illness, independent living, social relationships, physical senses and psychological wellbeing [35]. The AQoL instrument assesses the quality of life over five domains including illness, independent living, social relationship, physical senses and psychological wellbeing. The utility score for each dimension and an overall utility score range from 0 and 1, with 0 representing the worst health and 1 representing perfect health
*Physical activity level* will be assessed using The Incidental and Planned Exercise Questionnaire (IPEQ) for older people [36]. The IPEQ includes 10 questions that estimate physical activity during the last week which cover the frequency and duration of planned activity (planned exercise and walks) and incidental activities (casual day-to-day activities). The score was derived from multiplying the frequency score and duration score to create a total duration for incidental and planned activity as well as an overall total score. Total time spent will be summed across all components and expressed as hours per week as detailed in Delbaere et al. [36]
*Fear of falls* will be assessed using the Falls Efficacy Scale-International (Short FES-I) questionnaire [37]. The FES-I consists of seven items on Likert scale that score the participant’s level of concern regarding the possibility of falling when performing certain daily activities. The total score ranges from 7 (not concerned) to 28 (severe concern)
*Participant satisfaction* with the exercise program will be assessed at the completion of the 8-week exercise program using the Short Assessment for Patient Satisfaction measure (SAPS) [38]. The SAPS is a seven-item instrument that is used to assess patient satisfaction with their treatment. For the purposes of the present study, the phrases “treatment/care” will be changed to “exercise program” and “physician/other health professional” will be changed to “exercise leader/instructor.” The instrument has a 5-point Likert scale format, ranging from “very satisfied” to “very dissatisfied” or “strongly disagree” to “strongly agree.” Overall score ranges between 0 and 28 when 0 represents dissatisfaction and 28 represents great satisfaction

## Statistical analysis approach

Data collected for feasibility and safety will be analyzed using descriptive statistics (mean, standard deviation, and proportion) as follows: the percentage of participants who complete the intervention, overall percentage of sessions attended, number of participants who dropout, number of sessions and or number of exercises stopped due to pain, and any adverse event or incident that prevented the participant from completing the prescribed exercise.

Reported pain level will also be analyzed using descriptive statistics as follows: pain level during the exercise program, 2 h and 24 h after a session, any substantial increase in pain level to more than 7/10 or increase by 3 points, and overall pain level before, and at the completion of, the program.

To determine statistical trends of effectiveness, analyses of the selected outcomes, such as pain, strength, balance, physical function and executive functions, will be performed to assess the changes within and between groups over time (pre-post). Therefore, repeated measure analysis of variance (ANOVA) with factors of intervention (HSR, HSRTB, control) and time (pre-post intervention) will be used. This data will be used to determine power calculations for a fully powered future trial on the main outcomes investigated.

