Exercise interventions that focus on balance exercises have been shown to be effective in reducing falls for older people [6]. However, there is no evidence to suggest that current fall-prevention programs will be effective for people with knee OA. Moreover, existing exercise-based fall-prevention programs mainly focus on maintenance of balance and do not focus on training the neuromuscular elements required to arrest a fall. The neuromuscular elements required to arrest a fall are more impaired in people with knee OA compared to their asymptomatic counterparts [4]. To recover balance from falling, adequate muscle force and joint power generation is required [7]. This is adversely affected by OA. Hence, these unique factors and the associated pain must be taken into account in the design of fall-prevention strategies in this high-risk group. Consequently, development of an exercise approach aimed at reducing falls that is specifically designed to address these neuromuscular factors for people with knee OA is essential.

In this study we aim to examine the feasibility, safety and patient satisfaction of a high-speed resistance-training program, with and without balance exercises, in people with knee OA compared to a control group. Given the pain associated with knee OA, it is crucial to determine what effect high-speed resistance training that focuses on muscle power has on knee pain. This is of particular importance as this mode of exercise may potentially increase impact load on the knee joint due to the rapid and powerful movements involved. Therefore, feasibility and safety of the proposed exercise intervention must be assessed to determine if this exercise approach is safe to prescribe for those with knee OA. The effect of the exercise interventions on strength, physiological and functional risk factors for falls, pain, and executive function will also be assessed to provide data to support a sample size calculation for a fully powered trial.

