#### Participants

Participants aged 60–90 years with knee OA who have had a fall in the previous 12 months, or who are concerned about having a fall, will be recruited. Clinical diagnosis of knee OA based on the American College of Rheumatology will be used [9].

Inclusion criteria: participants will need to have had knee pain for at least 6 months and experience current average pain of at least 3 (on an 11-point Numerical Pain Rating Scale (NRS)) and be able to ambulate independently (with no more than a single-point stick used for ambulation). A total of 30 participants will be recruited (10 per group).

In addition to the above criteria, participants will also have to have one of the following criteria indicating increased risk of falling: (1) have had at least one fall in the past 12 months and (2) have limited their activity level due to concern about falling. Including people who are concerned about falling (with or without falls) will increase recruitment, and maintain a group at increased risk of falls, as activity limitation is often associated with reduced balance and mobility [10].

Participants will be excluded from this study if they have: (1) any uncontrolled nonmusculoskeletal conditions that would make testing difficult and uncomfortable such as chronic obstructive airways disease and/or congestive heart failure, (2) a pre-existing neurological condition that affects lower-limb strength, balance and or ambulation (e.g., polio, stroke), (3) any uncontrolled musculoskeletal or orthopedic conditions that may affect ambulation (e.g rheumatoid arthritis), (4) current involvement in a structured resistance-training and/or an organized balance-training program more than once a week, (5) any documented medical condition or physical impairment that is deemed by the medical practitioner to contraindicate their inclusion and (6) mild cognitive impairment or dementia determined by a score of less than 25 using the Saint Louis University Mental Status (SLUMS) test [11].

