## Outcome measures

### Feasibility and safety outcomes (primary measures)

Data for feasibility and safety will be analyzed as follows: percentage of participants who complete the intervention, overall percentage of sessions attended, number of participants who dropout due to reasons related to the exercise program or the overall research project, number of sessions and or number of exercises stopped due to pain, any adverse event or incident that stops the participant from completing the prescribed exercise.

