## Discussion

With the expected increase in the aging population and the number of people who suffer from knee OA, it is inevitable that falls and injuries experienced in this group will substantially rise. The reduction of mobility, injury and health-related quality of life associated with falls will have profound social and economic consequences into the future. The area of research in people with knee OA has been poorly studied despite the higher falls prevalence in this patient group [1–3]. The research project outlined in this protocol paper is the first step in addressing this deficit and will provide high-quality evidence for the safety and potential effectiveness of appropriate exercise programing for people with knee OA.

Balance exercises are key exercises recommended for fall prevention. Pain is a commonly reported barrier for not participating in exercise programs for people with OA; hence, carefully designing and evaluating an exercise intervention to address knee pain is crucial in order to develop safe, acceptable and effective fall-prevention interventions in this high-risk group. This study will be the first to provide outcomes that are critical to inform the development of an exercise-based fall-prevention intervention that is specifically designed to address the neuromuscular deficit associated with the increased risk factors for falls for people with knee OA. Consequently, the results of this pilot randomized controlled trial are essential to the design of a future, large, fall-prevention randomized controlled trial to reduce falls in this high-risk group.

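### The safety conclusion promised from 20 exercisers is stronger than a descriptive summary of that size can support; add exact intervals and call the evidence preliminary

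*Protocol article*

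**What the plan says.** The article labels its first outcome block "Feasibility and safety outcomes (primary measures". The items are "percentage of participants who complete the intervention, overall percentage of sessions attended", dropouts for reasons tied to the exercise or the project, sessions or exercises stopped for pain, and adverse events or incidents that prevent completion of an exercise.

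The Statistical analysis approach section fixes how these are summarised: "Data collected for feasibility and safety will be analyzed using descriptive statistics (mean, standard deviation, and proportion". It also describes pain during sessions and at 2 h and 24 h afterwards. It mentions no interval.

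On size, the Participants section states: "A total of 30 participants will be recruited (10 per group". Two of the three groups exercise.

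On purpose, the Background says that feasibility and safety "must be assessed to determine if this exercise approach is safe to prescribe for those with knee OA". The Discussion says the project "will provide high-quality evidence for the safety and potential effectiveness of appropriate exercise programing for people with knee OA".

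The sections on exercise progression, pain documentation and adverse events define in advance, with numbers, what counts as a substantial rise in pain, when an exercise is stopped, and when an adverse event is deemed to have occurred. These rules act on one participant or one exercise.

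**The concern.** The Background asks the primary outcome to settle whether the program can be prescribed safely, and the Discussion grades the resulting evidence as high quality. The analysis that feeds both is a set of means, standard deviations, counts and proportions from 10 people per exercise arm. A proportion shown without its uncertainty does not tell the reader how little so small a group can exclude.

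What is at stake is the main conclusion. Few or no events among 20 people would sit beside a stated intention to decide on safety, although a sizeable true risk would still be compatible with the data. The Background itself notes that rapid, powerful movement may increase load on the knee, so over-reading a clean result would matter here.

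**Working it through.** **Inputs.** From the Participants section: 30 in total, 10 per group; 3 × 10 = 30 agrees. Exercisers: 2 × 10 = 20. Sessions per exerciser, from the Procedure section: 2 per week × 8 weeks = 16, which agrees with the phases in Table 1 (4 + 6 + 6 = 16). The article gives no precision target, expected rate or derivation for the 30, so there is no such figure to reproduce.

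**Zero events.** The exact (Clopper-Pearson) two-sided 95% upper limit for 0 of n is 1 − 0.025^(1/n).
- n = 20: 1 − 0.025^(1/20) = 1 − 0.8316 = 16.8%
- n = 10: 1 − 0.025^(1/10) = 1 − 0.6915 = 30.8%

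**Other counts.** For x of n, the lower limit is the 0.025 quantile of Beta(x, n − x + 1) and the upper limit is the 0.975 quantile of Beta(x + 1, n − x). The counts are examples, not predictions.

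| Observed | Exact 95% interval |
|---|---|
| 1/20 with an event | 0.1% to 24.9% |
| 3/20 with an event | 3.2% to 37.9% |
| 16/20 complete (80%) | 56.3% to 94.3% |
| 8/10 complete (80%) | 44.4% to 97.5% |

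**Chance of missing an event entirely.** This is (1 − p)^n for a true per-participant risk p. The article gives no p, so the values below are assumptions shown over a range.

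| True risk p | No event in 20 | No event in 10 |
|---|---|---|
| 1% | 81.8% | 90.4% |
| 2% | 66.8% | 81.7% |
| 5% | 35.8% | 59.9% |
| 10% | 12.2% | 34.9% |

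**Attendance is a different kind of quantity.** Twenty exercisers with 16 sessions each give 20 × 16 = 320 person-sessions, but sessions within a person are correlated. With within-person correlation r, the effective number is 320 / (1 + 15r). This is 320 if r = 0 and 320 / 16 = 20 if r = 1. A binomial interval on 320 sessions assumes r = 0 and is too narrow whenever attendance habits differ between people.

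**The case against.** The strongest reply is that this is a pilot and is described as one. Its aim is to examine feasibility and safety, the Discussion calls the project a first step in the same sentence that claims high-quality evidence, and the results are meant to inform a later large trial. Descriptive statistics are the usual analysis for that purpose. All of this stands, and neither a formal test nor a larger sample is asked for.

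A reader might go further and infer that the program has no way to fail, because no completion, attendance or event rate is named that would count against it. The document does not support that reading. A journal article may leave progression values and intervals to the full protocol or the analysis plan, so their absence here is not in itself an error. Safety events are defined beforehand with numerical pain rules, and dropouts, stops and adverse events are all to be reported. A bad result would be visible and could not easily be relabelled. What those rules do not do is say how many such events would make the program unsafe or infeasible.

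A reader might also infer that the team plans to present zero events as proof of safety. Nothing says so. Zero pain-related events is not even the expected outcome, since mild to moderate pain during exercise is anticipated.

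What the reply does not answer is the stated strength of conclusion. An unseen analysis plan could add intervals, but it could not make 20 exercisers yield high-quality safety evidence.

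**Conclusion.** The point holds as a mismatch between claim and design. The Background and the Discussion state a decision and a grade of evidence that 10 people per exercise arm, summarised descriptively, cannot deliver. Even the most favourable safety result leaves a true risk of up to 16.8% (about one in six) not excluded across both programs, and up to 30.8% in either one. An 80% completion rate in 20 people is known only to within 56% to 94%.

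These figures assume that 10 people per exercise arm are reached and all contribute, that participants are independent, and, for the pooled figures, that the two programs share one underlying rate. Fewer participants would widen every interval. The pooled assumption is open to question because one program adds balance exercises, so the by-arm figures matter as well.

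The trial remains valid as a pilot. What should change is how its primary result is reported and how strongly it is described.

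**What to change.** 1. In the Statistical analysis approach, add exact 95% intervals, by exercise arm and for the two exercise arms pooled, for the proportions whose unit is the participant: completion, dropout, any pain-related stop and any adverse event.
2. For sessions attended, compute each participant's attendance percentage and give an interval for the mean of these. Do not put a binomial interval on the session total.
3. Reword the Background and Discussion so that the trial provides preliminary evidence on safety. State that zero affected participants among 20 exercisers would still leave a risk of up to 16.8% not excluded. In the final report, quote the limit for the count actually observed.
4. Secondary: if the result is to decide whether the large trial goes ahead, the team should set its own progression values for the primary measures before data are seen, or cite the document where they already stand.

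The cost is a few lines of text, intervals from standard software and a more modest safety claim. Sample size, treatment and data collection do not change.
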